### Data collection

Data collected during the study will be recorded on REDCap, a secure web-based application for databases. Attendance at surveillance scans and HCC outcomes will be entered onto the database. At the end of the study (2 years), the following data will be extracted for analysis: age, sex, ethnicity, native language, Index of Multiple Deprivation quintile (based on patient’s home postcode), aetiology of liver disease, surveillance episodes, diagnosis of HCC and reasons for removal from surveillance pathway, if any.

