**Methods and analysis:**

This is a two-arm randomised controlled trial that will recruit 652 participants. Participants will be patients with chronic liver disease or cirrhosis, who are eligible for HCC surveillance as defined by criteria from the National Institute for Health and Care Excellence and European Association for the Study of the Liver. Participants will be randomised (in a 1:1 ratio) to receive either (a) a mailed surveillance invitation or (b) a mailed invitation plus telephone call reminder from a PN 1 week prior to the appointment. The primary objective is to evaluate the impact of PNs and mailed invitations on attendance rates. Secondary objectives include rates of diagnosis of early-stage HCC among patients undergoing surveillance and cost-effectiveness of each arm.

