### Trial objectives

#### Primary objective

The primary objective is to evaluate the effect of bespoke mailed invitations and the addition of PN on the rate of patient attendance at surveillance appointments at each 6 monthly interval over a 2 year period.

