### Eligibility criteria

Participants will be recruited from a local patient database held by the liver care team at Imperial College Healthcare NHS Trust. A generic screening process will be undertaken through electronic chart review where the following data items will be collected: patient age, patient sex, home address postcode, whether the patient is a native English speaker and aetiology of liver disease. The database will only be accessed by the direct care team to identify potential trial participants.

Subjects will need to be deemed eligible for HCC surveillance as defined by NICE and EASL guidelines. This includes adults with liver cirrhosis classified as Child–Pugh A or B, and cirrhotic patients with Child–Pugh C disease awaiting liver transplantation.^18^ Comprehensive inclusion and exclusion criteria are outlined in table 1.^7^ The study aims to recruit 652 eligible participants.

**Table 1 T1:** Inclusion and exclusion criteria

Inclusion criteria	Exclusion criteria
Age ≥18 years	Known previous or current diagnosis of HCC
Good or moderate performance status (ECOG, category 0–2)	Patients with Child–Pugh stage C cirrhosis who are not a candidate for liver transplantation
Child–Pugh stage A or stage B cirrhosis	Previous liver transplant
Child–Pugh stage C cirrhosis, awaiting liver transplantation	Score of >7 on the Clinical Frailty Scale
Non-cirrhotic chronic hepatitis B patients at intermediate or high risk of HCC (according to PAGE-B classes for Caucasian subjects, respectively 10–17 and ≥18 score points)	

ECOG, Eastern Co-operative Oncology Group; HCC, hepatocellular carcinoma.

The study will run between 2 January 2025 and 2 July 2027, and participant recruitment commenced on 1 February 2025.

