### Statistical analysis

Descriptive statistics will be used to summarise baseline patient characteristics, primary and secondary outcomes from the two study groups. Continuous variables will be reported using number of observations, arithmetic mean, SD, median and minimum and maximum values; categorical variables will be summarised by frequencies and percentages. A two-way repeated measures analysis of variance will be performed, with time as a repeated factor, to compare the two intervention arms with respect to the primary outcome. Intention-to-screen analyses will be undertaken. Additionally, cost-effectiveness analysis will be performed using the return on investment (ROI) tool developed by Public Health England. The interactive ROI Tool can help estimate ROI, cost savings and health outcomes from specific public health interventions to guide authorities and policymakers to invest in initiatives that maximise health and economic benefits.^19^

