### Sample size and power calculation

The target sample size is 326 participants in each trial arm. With a sample size of 652 participants in total, at an alpha of 0.05, the study has 85% power to detect a 10% absolute difference in surveillance rates between the intervention and control groups. This assumes a baseline surveillance completion rate of 10% in standard care, derived from a similar RCT in the USA comparing the effect of mailed outreach and PN on HCC surveillance participation.^16^

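### Attendance before randomisation is not identified in either data list and has no place in the planned primary model, so the arm comparison gives up precision

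*Protocol article*

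**What the plan says.** All references are to the protocol article.

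- **Eligibility criteria.** Participants come from the liver team's local database. "A generic screening process will be undertaken through electronic chart review", and five items are collected: age, sex, postcode, whether English is the native language, and aetiology.
- **Data collection.** The end-of-study extraction covers "age, sex, ethnicity, native language, Index of Multiple Deprivation quintile (based on patient’s home postcode), aetiology of liver disease, surveillance episodes, diagnosis of HCC" and any reasons for removal from the pathway. The surveillance-episodes item has no time window. The text just before it concerns data recorded during the study, and the Outcomes section counts episodes within the study period.
- **Statistical analysis.** The primary comparison is a two-way repeated-measures analysis of variance, "with time as a repeated factor, to compare the two intervention arms with respect to the primary outcome". No baseline value or other covariate is named.
- **Sample size and power calculation.** "The target sample size is 326 participants in each trial arm"; "at an alpha of 0.05, the study has 85% power to detect a 10% absolute difference in surveillance rates". "This assumes a baseline surveillance completion rate of 10% in standard care", a figure taken from a US trial.
- **Primary objective.** Attendance is assessed "at each 6 monthly interval over a 2 year period", which gives four intervals.

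**The concern.** The outcome is a repeated behaviour: turning up for a six-monthly scan. Many participants are likely to have been offered such scans before the trial. How often they attended is then the natural baseline measurement, and it would be expected to predict later attendance better than age, deprivation or aetiology, all of which are listed.

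Three things are at stake:

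- **Precision.** A between-patient comparison that ignores a strong baseline predictor has a larger standard error than it needs.
- **Visibility of imbalance.** If one arm happens to contain more habitual attenders, nobody can see it.
- **Context.** Both arms receive the bespoke invitation, so no arm shows attendance under ordinary appointments. The assumed 10% is imported, while the article itself cites about 20% attending regularly (Abstract) and a pooled 24% (Introduction).

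Covariate choice can be left to an analysis plan. However, that plan can adjust only for data that are collected, and this article sets out the extraction list.

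**Working it through.** **1. The plan's own figure.** Inputs: 10% v 20%, 326 per arm, alpha 0.05 (two-sided assumed). Power = Φ{[0.10 − 1.96·√(2·0.15·0.85/326)] / √[(0.10·0.90 + 0.20·0.80)/326]} = Φ{(0.10 − 0.0548)/0.0277} = Φ(1.63) = 94.9%. The stated 85% is not reproduced; 228 per arm would give it. That mismatch is a separate matter. It is shown here because it sets the base against which a gain in precision is judged.

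**2. Gain from adjusting, as a formula.** Assume equal variance σ² and a common correlation ρ between any two intervals of the same patient, with two intervals known before randomisation and four after.

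- Variance of the prior mean: σ²(1+ρ)/2
- Variance of the four-interval study mean: σ²(1+3ρ)/4
- Covariance of the two means: ρσ²
- Variance cut for the four-interval mean: 8ρ²/[(1+ρ)(1+3ρ)]
- Variance cut for one study interval: ρ²/[(1+ρ)/2] = 2ρ²/(1+ρ)

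The four-interval mean is what the arm main effect of the planned analysis compares.

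**3. Numbers put in.** ρ is an assumption; the article gives none.

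| ρ | Four-interval mean | Single interval |
|---|---|---|
| 0.1 | 0.08/1.43 = 5.6% | 0.02/1.1 = 1.8% |
| 0.2 | 0.32/1.92 = 16.7% | 0.08/1.2 = 6.7% |
| 0.3 | 0.72/2.47 = 29.1% | 0.18/1.3 = 13.8% |
| 0.5 | 2.00/3.75 = 53.3% | 0.50/1.5 = 33.3% |

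A simulation gave slightly lower four-interval cuts: 5%, 15%, 27% and 50%. It used 326 per arm, beta-distributed patient propensities with mean 20% or 30%, a 10-point effect and 300 runs per setting. Taking these lower values, the equivalent in extra participants is 652·[1/(1−v) − 1], where v is the cut: 34, 115, 241 and 652. For a single interval the same formula gives 12, 47, 105 and 326.

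For attendance at all four scans, the core of the regular-attendance outcome (8-month rule ignored), the same beta model with mean 20-30% gives cuts of about 0.5-1%, 3-4%, 8-10% and 26-28%.

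**4. Patients without a history.** If a fraction f are new to surveillance and form their own category, the cut becomes (1−f) times the figure above. With f = 40% (an assumption), the four-interval cuts fall to 3.4%, 10.0%, 17.5% and 32.0%.

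**5. What this does to power.** Effective n is 326/(1−v). Two cuts within the single-interval range are shown.

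| Contrast | Unadjusted | 9% cut | 25% cut |
|---|---|---|---|
| 10% v 20% | 94.9% | 96.5% | 98.6% |
| 24% v 34% | 80.5% | 84.0% | 90.3% |

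**6. Chance imbalance.** The 95% range for the arm difference in the proportion with prior attendance is ±1.96·√[2q(1−q)/326]. This is ±4.6 points if q = 10%, ±6.6 if q = 24% and ±7.7 if q = 50%, against a target difference of 10 points in the outcome.

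**The case against.** The strongest case against is that this is a condensed article. Covariates, the baseline table and the data dictionary usually sit in the full protocol or analysis plan, and nothing quoted above is false. That stands as a limit on the claim: the absence of a baseline term is firm only for the analysis as the article describes it. It does not remove the point, because the article gives explicit data lists and a named model, and both can be improved at low cost.

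Several stronger readings are tempting, and the document does not support them:

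- *Prior attendance is definitely not collected.* The surveillance-episodes item is undated. On-study scans is the likelier reading, not a stated one.
- *The charts already hold it.* The article says only that there is a liver-team database and a chart review. That past scans are recorded there is a plausible inference.
- *It is the baseline value of the primary outcome.* The Introduction describes current UK booking as ad hoc, whereas trial appointments run through a call-and-recall system. A bare count of past scans therefore mixes patients who were not booked with patients who did not attend. This weakens the assumed correlation, and it is why booked scans should be recorded where possible.
- *The comparison is biased.* It is not. Randomisation protects it, and the unadjusted standard error already allows for chance imbalance.
- *The four-interval gain applies to every outcome.* It is the most favourable case. The gain is smaller for a single interval and for regular attendance.

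It is also fair to say that on the stated 10% v 20% contrast power is already high, so the gain matters mainly if local attendance is above 10%.

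**Conclusion.** The concern holds in limited form. Attendance before randomisation is not identified among the screening or extraction items, and the planned analysis has no baseline term. The cost is lost precision and an unseen imbalance, not bias.

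The size rests wholly on assumption. With within-patient correlations of 0.1 to 0.5 and two prior intervals known for everyone, the variance cut is about 5-50% for the four-interval mean and about 2-33% for a single interval. It shrinks in proportion to the share of newly eligible patients, and further where patients were never booked. At the low end the gain is trivial; at the high end it is worth several hundred participants.

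A reader might also infer that the field would validate or refute the 10% assumption. It would describe prior local uptake, but it is only a rough check, because booking before the trial differed from booking within it.

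**What to change.** 1. In Data collection, state whether the surveillance-episodes item covers the period before randomisation. If it does not, add scans attended and, where recorded, scans booked in the 12 months before randomisation, with a separate category for patients not yet under surveillance.
2. Report this field by arm with the baseline characteristics.
3. Prespecify it as a covariate in the primary model, before any comparison of outcomes by arm. Recruitment has begun, but the field is retrospective and can still be added.
4. Use it to describe prior local uptake, and say that it is not a direct test of the 10% assumption.

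The cost is a small retrospective chart extraction for 652 patients, assuming the Trust's records hold past scans. A check on a few records would settle that before the field is fixed. No change to recruitment, allocation or the interventions is needed.

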### Statistical analysis

Descriptive statistics will be used to summarise baseline patient characteristics, primary and secondary outcomes from the two study groups. Continuous variables will be reported using number of observations, arithmetic mean, SD, median and minimum and maximum values; categorical variables will be summarised by frequencies and percentages. A two-way repeated measures analysis of variance will be performed, with time as a repeated factor, to compare the two intervention arms with respect to the primary outcome. Intention-to-screen analyses will be undertaken. Additionally, cost-effectiveness analysis will be performed using the return on investment (ROI) tool developed by Public Health England. The interactive ROI Tool can help estimate ROI, cost savings and health outcomes from specific public health interventions to guide authorities and policymakers to invest in initiatives that maximise health and economic benefits.^19^

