## Methods and analysis

### Study design

VIGILANT is a RCT with two parallel groups, aiming to investigate the effect of mailed invitations with or without PN to improve the rate of HCC surveillance uptake over 2 years. Adults aged ≥18 years, at risk of developing HCC and suitable for HCC surveillance will be eligible to participate in the study. Surveillance uptake will be quantified based on patients’ attendance at their surveillance imaging appointments. In standard clinical practice in the UK, patients receive a random appointment time and date through the post, with subsequent provisions to reschedule if they are unable to attend the initial proposed appointment. To investigate the effect of enhanced outreach, trial participants will be randomised to one of the two following arms using a computer-generated number (figure 1):

Bespoke surveillance invitation, consisting of a one-page mailed invitation and an informational postcard.Bespoke surveillance invitation plus PN, which comprises a scripted PN telephone call 1 week prior to surveillance appointment (in the event of non-attendance, a further follow-up PN call).

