### Outcomes

The primary outcomes of the study are (i) attendance rates at each 6 month interval and (ii) proportion of patients in each trial arm attending HCC surveillance regularly. Frequency of attendance at surveillance scans will be categorised into three groups: regular, infrequent and non-attendance.

Regular attendance is defined as fulfilment of four or more HCC surveillance episodes over the study period, with no more than 8 months interval between surveillance appointments.Infrequent attendance is defined as attendance at some HCC surveillance appointments, but less than four episodes, or with intervals greater than 8 months between surveillance appointments.Non-attendance is defined as no attendance at any HCC surveillance appointments over the study period.

Secondary outcome measures are (i) proportion of patients in each arm diagnosed with early-stage HCC compared with late-stage HCC and (ii) comparative cost of interventions.

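### The one named primary analysis, a repeated-measures ANOVA, cannot be applied to regular attendance and is an unsuitable model for yes/no interval attendance

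*Protocol article*

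**What the plan says.** The Outcomes section of the protocol article begins with "The primary outcomes of the study are (i) attendance rates at each 6 month interval and (ii) proportion of patients in each trial arm"; the second of these is the share who attend regularly. Regular attendance means "fulfilment of four or more HCC surveillance episodes over the study period, with no more than 8 months interval between surveillance appointments". It is one level of a whole-study classification: "Frequency of attendance at surveillance scans will be categorised into three groups: regular, infrequent and non-attendance". Study design adds: "Surveillance uptake will be quantified based on patients’ attendance at their surveillance imaging appointments". So the interval outcome is attended or not attended.

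The Statistical analysis section promises descriptive summaries of the outcomes by group. It then names one inferential method for attendance, "A two-way repeated measures analysis of variance will be performed, with time as a repeated factor, to compare the two intervention arms", and applies it "with respect to the primary outcome", in the singular. It also states "Intention-to-screen analyses will be undertaken", without defining the term, and gives a tool for the cost-effectiveness work. No other test or model for attendance appears.

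Data collection lists "reasons for removal from surveillance pathway, if any" among the items extracted at the end of the study, so the plan allows for participants leaving surveillance.

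**The concern.** Three things do not fit together.

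- Two outcomes are primary, but the single named method needs a series of measurements per participant. Regular attendance is one category per participant.
- The outcome that does form a series is binary, while ANOVA is a model for a continuous response with constant variance.
- Classical repeated-measures ANOVA uses only participants with a complete series. How that sits with an intention-to-screen analysis depends on how intervals after removal are coded, and the article does not say.

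The first matters most. Followed as written, one of the two primary outcomes has no between-arm test. Allocation is not blinded, recruitment began in February 2025, and data are extracted at study end. Unless the text is corrected, that test could be chosen with the results in view.

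**Working it through.** **The plan's own figure.** The article gives no figure for the ANOVA. The nearest is 85% power with 326 per arm for a 10-point difference from 10% (Sample size and power calculation). Taking 10% against 20%, two-sided 0.05 (sidedness is not stated), with a pooled null variance:

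- null standard error √(2 × 0.15 × 0.85 / 326) = 0.02797
- alternative standard error √((0.09 + 0.16) / 326) = 0.02769
- power = Φ[(0.10 − 1.96 × 0.02797) / 0.02769] = Φ(1.63) = 94.9%

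So 85% does not reproduce from the stated inputs. The need for 85% is 228 per arm, and an unstated 30% loss allowance would give 228 / 0.70 = 326. That is a separate matter, and nothing below depends on it.

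**Step 1: match method to outcome.**

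| Primary outcome | Values per participant | Type | Can the named ANOVA be applied? |
|---|---|---|---|
| Attendance at each 6-month interval | four over 2 years | yes/no | It can be computed, but the model is for continuous data |
| Regular attendance | one | category | No: there is no repeated factor |

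**Step 2: can the interval result stand in for regular attendance?** Assume one appointment per interval, with the 8-month limit met by anyone attending all four. Let attendance be 50% at every interval.

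- All-or-none attendance: 50% attend all four.
- Independent visits: 0.5⁴ = 6.25% attend all four.

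If one arm behaved the first way and the other the second, regular attendance would differ by 50 − 6.25 = 43.75 points, while the ANOVA would see no arm effect. This is a deliberate extreme.

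A milder case comes from simulating four correlated yes/no attendances per participant (logistic model, normal random intercept with SD 2, an assumption; 326 per arm; 4,000 runs). Interval attendance of 10% against 20% gave 1.3% against 4.3% attending all four. Interval attendance of 40% against 50% gave 14.9% against 22.5%. A 10-point interval difference thus became about 3.0 and 7.6 points.

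**Step 3: does ANOVA on 0/1 data give false positives?** With complete data the between-arm test equals a t-test on each participant's mean attendance. Rejection rates under no arm difference, in the same simulation:

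| Attendance in both arms | Arm | Arm-by-interval |
|---|---|---|
| 10% throughout | 4.9% | 5.0% |
| Falling from 60% to 40% | 5.4% | 5.1% |

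Monte Carlo standard error: √(0.05 × 0.95 / 4000) = 0.34 points. None of these departs from 5%. The arm-by-interval result holds for the assumed correlation pattern; the arm test does not need sphericity.

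**Step 4: intention-to-screen.** There are two codings of intervals after removal, and the article chooses neither.

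- *Missing.* Incomplete participants are dropped. The article gives no exit rate. At an assumed 5% to 10% a year, 1 − 0.95² = 9.75% to 1 − 0.90² = 19% leave within 2 years, so 652 × 0.9025 = 588 to 652 × 0.81 = 528 remain. This is somewhat pessimistic, because an exit after the fourth appointment costs no interval. With an assumed 20% lost at random (about 522 left), simulated power for 40% against 50% interval attendance fell from 93.7% to 88.3%.
- *Not attended.* Every randomised participant has four values, and nobody is dropped.

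**The case against.** The strongest reply is that this is a condensed article. The Primary objective speaks of attendance at each 6-monthly interval, so the ANOVA was probably meant for that outcome, with the test for regular attendance left to a fuller document. That is a fair reading of intent. It does not remove the point, because the article makes regular attendance primary and then fixes a method for the primary outcome that cannot handle it. This is a mismatch in what is stated, rather than a missing detail.

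Several other replies stand, and they rule out stronger readings that a reader might infer:

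- *The ANOVA contradicts intention-to-screen.* Not shown. Scoring an absent interval as not attended is a natural coding and leaves no missing cell. Dropping participants is one possibility, and the 528 to 588 range applies only under it.
- *The ANOVA will give false positives.* Step 3 shows no sign of this for the arm comparison.
- *The ANOVA cannot express the powered difference.* Not so for interval attendance: cell means of 0/1 data are proportions, so its contrasts are absolute differences. It does not give the difference in regular attendance. Whether the sample size was built on regular attendance is only an inference from the article's reference to a completion rate.
- *Regular attendance will go unreported.* Percentages by group are promised. What is lacking is a named between-arm comparison.

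**Conclusion.** The point holds in a limited form. That the named method cannot be applied to regular attendance rests on the article's own definitions and needs no assumed figure. Step 2 shows that interval attendance does not determine regular attendance, so the ANOVA cannot serve for both outcomes.

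For interval attendance, the ANOVA is an unsuitable model for binary data, with no demonstrated harm to the arm test when data are complete and 326 are in each arm.

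On intention-to-screen, the two statements are not reconciled, and the size of any loss depends on an exit rate and a coding that the article does not give. The choice is not neutral. Under Mailed invitations, the repeat scan follows a normal result and an abnormal one leads to further investigation. Only attenders can have an abnormal surveillance scan, so some exits may follow from attending. Dropping such participants removes attenders; scoring their later intervals as not attended counts them as absent.

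**What to change.** In the Statistical analysis section:

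1. **Regular attendance.** Compare the proportions between arms in all randomised participants, and report the risk difference with its 95% CI.
2. **Interval attendance.** Replace the ANOVA with a binary repeated-measures model (GEE with robust standard errors, or mixed logistic) containing arm, interval and arm-by-interval. Report per-interval risk differences with CIs, taken from the fitted probabilities. With a mixed model, average these over the random effect.
3. **Intervals after removal.** State how intervals after death, transplant, HCC diagnosis or other removal are counted, so that all randomised participants enter the analysis. Item 2 does not settle this by itself, since a model fitted to available intervals still treats those after exit as missing.

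Covariate adjustment is optional. The cost is revised wording and slightly more analysis work, with no new data. The change should be dated before outcome data are compared by arm.

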**Trial registration number:**

NCT06635694.

STRENGTHS AND LIMITATIONS OF THIS STUDYPragmatic randomised controlled trial design enabling evaluation of the effectiveness of studied interventions in a real-world setting.This trial adopted a co-design process in designing the mailed surveillance invitations disseminated to patients to place patients’ needs at the crux of the proposed interventions—a novel approach not previously used in hepatocellular carcinoma (HCC) surveillance studies.Study targets an ethnically diverse patient population, increasing applicability to regions across the UK.The use of outreach media may exclude marginalised and deprived populations that are typically hard-to-reach and disproportionately represented in the HCC surveillance target population.

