### Study procedures

Study participants will be randomised into one of the two trial arms:

Mailed invitations only.PN in addition to mailed invitations.

Randomisation will be carried out centrally using a computer-generated sequence. Concealed allocation will be used to reduce the risk of selection bias. Due to the nature of the interventions, no blinding will be employed.

The current surveillance recommended by NHS England comprises regular 6 monthly liver ultrasound scans for eligible patients.^7^ In routine clinical practice, the surveillance ultrasound scan will be requested by the subject’s responsible clinician. Ensuing ultrasound appointments will be flagged and booked by the clinical team using a bespoke call-and-recall system (RedCap).

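### The primary model is fixed as arm by time with no baseline covariates, though plausibly prognostic variables are already recorded at screening: a modest, nearly free gain in precision is left unused

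*Protocol article*

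**What the plan says.** Under Statistical analysis, the article names the primary model: "A two-way repeated measures analysis of variance will be performed, with time as a repeated factor, to compare the two intervention arms". The factors are arm and time. The same section gives baseline variables one explicit role: "Descriptive statistics will be used to summarise baseline patient characteristics". It does not say that the arm comparison will be adjusted, and it does not say that it will not be.

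Under Eligibility criteria, the chart review at screening records "patient age, patient sex, home address postcode, whether the patient is a native English speaker and aetiology of liver disease". Under Data collection, the end-of-study extract for analysis includes "age, sex, ethnicity, native language, Index of Multiple Deprivation quintile (based on patient’s home postcode), aetiology of liver disease". Ethnicity appears in that extract but not in the screening list.

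Under Study procedures, the allocation method is described briefly: "Randomisation will be carried out centrally using a computer-generated sequence". Allocation is concealed and the trial is open. No stratification factor is named.

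Under Outcomes, the two primary outcomes are attendance at each 6-month interval and the proportion attending regularly. Each is yes/no for a given patient.

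**The concern.** When variables measured before randomisation predict the outcome, including them in the primary model reduces the residual variance and corrects for chance imbalance in those variables. The interval for the arm difference narrows without recruiting anyone. Here the candidate variables already exist for every screened participant, but the published model has no place for them.

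The article gives some indirect reason to expect them to matter. The Introduction lists difficulty travelling and poor understanding of surveillance among the patient-related causes of low uptake, and the strengths and limitations box says "The use of outreach media may exclude marginalised and deprived populations that are typically hard-to-reach". Deprivation quintile and native language are reasonable proxies for these barriers.

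Timing matters too. The trial is open, so a covariate list chosen after attendance by arm is visible would be open to doubt. Because the article already publishes a two-factor model, a later adjusted primary analysis would look like a departure unless it is declared in advance. At stake is some precision; validity is not affected.

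**Working it through.** **Inputs.** From the article: 326 per arm, alpha 0.05, a 10-point absolute difference, a 10% rate in standard care (Sample size and power calculation), and 1:1 allocation (Abstract). Assumed: a two-sided test, since sidedness is not stated, and R², the share of variance in attendance that the covariates explain, for which the article gives no value.

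**Step 1: the plan's own figure.** With d = p2 − p1, p̄ = (p1 + p2)/2, se0 = √[2p̄(1 − p̄)/n] and se1 = √{[p1(1 − p1) + p2(1 − p2)]/n}, power = Φ[(d − 1.96·se0)/se1].

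For 10% versus 20% with n = 326:
- se0 = √(0.255/326) = 0.02797
- se1 = √(0.25/326) = 0.02769
- power = Φ[(0.1 − 0.0548)/0.02769] = Φ(1.63) = 94.9%

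The article states 85%, which this does not reproduce. For 85% power, 228 per arm would suffice. A figure of 326 is matched only by inputs the article does not state, such as 228/(1 − 0.30) = 326 or a control rate near 19%. That mismatch is a separate matter; 94.9% is the starting point used here.

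**Step 2: effect of adjustment.** Adjustment multiplies the residual variance by about (1 − R²), so the effective n per arm is 326/(1 − R²):
- R² = 2%: 332.7 per arm, about 13 more participants in total
- R² = 5%: 343.2 per arm, about 34 more
- R² = 10%: 362.2 per arm, about 72 more

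Putting the effective n into the power formula, and 1.96·se1·√(1 − R²) for the 95% CI half-width:

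| Rates compared | Quantity | Unadjusted | R² 2% | R² 5% | R² 10% |
|---|---|---|---|---|---|
| 10% vs 20% (article) | Power | 94.9% | 95.2% | 95.8% | 96.6% |
| | Half-width, points | 5.43 | 5.37 | 5.29 | 5.15 |
| 20% vs 30% (assumed) | Power | 84.0% | 84.7% | 85.8% | 87.6% |
| | Half-width, points | 6.60 | 6.54 | 6.44 | 6.26 |
| 24% vs 34% (assumed) | Power | 80.5% | 81.3% | 82.4% | 84.4% |
| | Half-width, points | 6.92 | 6.85 | 6.75 | 6.57 |

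The higher control rates are shown because the 10% is for standard care, while the comparator here receives the bespoke invitation. The values 20% and 24% are uptake figures from the Abstract and Introduction. The article does not give them as the expected rate in the mailed-invitation arm.

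**Step 3: is the assumed R² range reasonable?** R² was computed as Var[p(X)]/[p(1 − p)] in a simulation with five covariates (age, sex, native language, deprivation quintile, aetiology), mean attendance from 10% to 55%, and assumed odds ratios:
- weak (1.1, or 0.9 to 0.95): R² about 0.2% to 0.5%
- moderate (1.3, or 0.6 to 0.85): about 2% to 6%
- strong (1.6, or 0.4 to 0.7): about 8% to 17%

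So 2% to 5% corresponds to moderate predictors and 10% to strong ones. At R² = 0.5% the effective n is 326/0.995 = 327.6 per arm, about 3 participants in total.

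The calculation treats one yes/no outcome per patient, which fits regular attendance directly and a single 6-month interval approximately.

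**The case against.** The strongest objection is scope. A covariate list is commonly left to the statistical analysis plan, which is not shown, and nothing in the article excludes adjustment. This has weight: the article cannot be faulted for silence alone. What remains is that it goes beyond silence, because it publishes a model with two named factors, and adjusting later would change that model.

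Second, the gain may be small. In the article's own scenario power is already 94.9% and rises by 0.3 to 1.7 points. With weak predictors it hardly moves. Prior attendance, plausibly a stronger predictor, is not among the listed variables. This stands, and it limits the point to a modest one.

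Some stronger readings are tempting but are not supported:
- A reader might infer that the variables are known to be prognostic. The article reports no association with attendance. The barriers it lists are not themselves recorded variables, and its remark on deprived groups concerns who outreach may fail to reach.
- A reader might infer that baseline data will be used only descriptively. The Data collection section says they are extracted for analysis, without limiting that use.
- A reader might infer that randomisation is unstratified. The brief description does not show this, since such detail is often left to the full protocol.

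**Conclusion.** The point holds as an efficiency recommendation. The published primary model names no baseline covariate, and suitable variables are already collected before allocation. A reader might go further and conclude that the planned comparison is biased or invalid. It is not: under 1:1 randomisation the unadjusted arm difference is unbiased.

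For assumed R² of 2% to 10%, the gain equals about 13 to 72 participants. Power rises by 0.3 to 1.7 points at 10% versus 20%, and by 0.7 to 3.6 points if the mailed-invitation arm attends at 20%. The description of the model and the arithmetic are secure. The size of the gain is not, because it rests wholly on R² and control rates that the article does not give.

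**What to change.** Before anyone has seen attendance by arm, state in the analysis plan that the primary model for both primary outcomes includes a short fixed list of pre-randomisation covariates: age, sex, deprivation quintile from the screening postcode, native-English status, aetiology, and any stratification factors used. Ethnicity should be added only if it is confirmed as recorded before allocation.

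Put the covariates into whichever model suited to binary attendance is adopted, for example a GEE or mixed logistic model; adding them to an ANOVA of yes/no data would not be the right form. Report the arm effect as a covariate-standardised risk difference with 95% CI, which keeps the absolute scale of the sample size section. Retain the unadjusted result as a sensitivity analysis.

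The cost is wording and a little extra analysis work. No new data, visits or participants are needed. The downside is that the effort yields almost nothing if the covariates predict attendance weakly.
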